## Abstract

For pancreatic masses, an evaluation of their vascularity using contrast-enhanced ultrasonography can help improve their characterization. This study was designed to evaluate the utility and safety of contrast-enhanced transabdominal ultrasonography (CE-TUS) and endoscopic ultrasonography (CE-EUS) in the diagnosis of pancreatic masses including solid or cystic masses. This multi-center comparative open-label superiority study is designed to compare Plain (P)-TUS/EUS alone with P-TUS/P-EUS plus CE-TUS/CE-EUS. Three hundred and one patients with a total of 232 solid pancreatic masses and 69 cystic masses were prospectively enrolled. The primary endpoints are to compare the diagnostic accuracy between P-TUS/P-EUS alone and P-TUS/P-EUS plus CE-TUS/CE-EUS for both the TUS and EUS of solid pancreatic masses, and to compare the diagnostic accuracy between P-EUS alone and P-EUS plus CE-EUS in cystic pancreatic masses. The secondary endpoints are to compare the diagnostic sensitivity and specificity of P-TUS/P-EUS alone and P-TUS/P-EUS plus CE-TUS/CE-EUS for pancreatic solid/cystic masses, and the accuracy of P-TUS alone and P-TUS plus CE-TUS for pancreatic cystic masses. Other secondary endpoints included comparing the diagnostic sensitivity, specificity, and accuracy of CE-TUS, CE-EUS and CE-computed tomography (CT) for solid/cystic pancreatic masses. The safety, degree of effective enhancement, and diagnostic confidence obtained with CE-TUS/CE-EUS will also be assessed.

## 1. Introduction

Pancreatic cancer is the fourth leading cause of cancer-related death in the USA and Japan, and the incidences of pancreatic cancer and related mortality have recently increased [1,2]. The National Cancer Center Japan reported that 37,677 people died of pancreatic cancer in Japan in 2020 [2]. Despite recent advances in diagnostic imaging modalities, most cases of pancreatic cancer are discovered at an unresectable stage for which the prognosis is poor, with a 5-year survival rate of approximately 11% [1]. This poor prognosis is mainly related to the difficulties associated with the diagnosis of pancreatic cancers at an early stage; early diagnosis is essential to ensure curative treatment and improve the prognosis of patients with pancreatic cancer [3].

For early stage I pancreatic cancer, Kanno et al. reported tumor detection rates of 67.3% for transabdominal ultrasonography (TUS), 65.8% for computed tomography (CT), 57.5% for magnetic resonance imaging (MRI), and 92.4% for endoscopic ultrasonography (EUS) [3]. Although TUS showed a similar diagnostic ability to CT and MRI for early pancreatic cancer, TUS is the simplest, most affordable, and most widely used modality, and can therefore be considered the most suitable modality for screening for pancreatic cancer. However, compared with other imaging modalities, including TUS, EUS provides superior spatial resolution for the early diagnosis of pancreatic cancer [4]. Despite this, plain TUS/EUS alone is limited in its ability to distinguish pancreatic cancer from non-neoplastic pancreatic masses because most solid pancreatic masses are detected as hypoechoic masses.

Pancreatic cystic tumors are frequency detected by cross-sectional imaging. Pancreatic cystic tumors can range from malignant to benign. In cystic tumors, intraductal papillary mucinous neoplasms (IPMNs) and mucinous cystic neoplasms (MCNs) have malignant potential. IPMNs are pancreatic cystic tumors that display a dilatation of the excretory pancreatic ducts and mucous production by papillary proliferation of the ductal epithelium. They commonly occur in the elderly. IPMNs are divided into the branch duct type, main pancreatic duct type, and mixed type. According to previous reports, the malignancy for main duct-type tumors ranges from 57% to 92% [5,6,7,8,9]. On the other hand, the malignancy rate for branch duct-type tumors is relatively low (6–46%) [10,11,12,13]. Therefore, in branch duct-type IPMNs, an assessment of the mural nodules is important for malignant transformation. Therefore, the presence of mural nodules ≥5 mm in size is identified as an important factor for making decisions on surgical intervention in the 2017 guidelines for IPMN [14]. MCNs are mucus-producing cystic tumors that are common in middle-aged women. All MCNs should be resected to prevent malignant changes. According to a previous report, the malignancy is 17.3% in resected MCNs [15]. On the other hand, serous cyst neoplasms (SCNs) are multilocular cystic tumors with serous content that consist of glycogen-rich clear cells. SCNs are generally considered benign. Therefore, differential diagnosis is important. On the other hand, EUS is one of the most reliable and efficient diagnostic modalities for pancreatic cystic tumors due to its superior spatial resolution compared with any other modality. However, it is sometimes difficult to diagnose markers of malignant transformation such as the presence of a mural nodule.

In this context, an assessment of the vascularity of masses is useful for the differential diagnosis of pancreatic masses detected on P-TUS/P-EUS. In clinical practice, contrast-enhanced TUS/EUS (CE-TUS/CE-EUS) has become increasingly used as an adjunctive method for the characterization of pancreatic tumors. Moreover, there are three advantages of CE-EUS over the other imaging methods. First, CE-TUS/CE-EUS can detect signals from microbubbles in vessels with a very slow flow and without Doppler-related artifacts compared to contrast-enhanced color and power Doppler TUS/EUS. Second, CE-TUS/CE-EUS has an advantage over contrast-enhanced MRI and CT in patients with contraindications in the use of contrast materials, such as in renal failure or contrast allergy, even though adverse reactions to contrast agents are rare in humans. Third, CE-TUS/CE-EUS allows real-time dynamic imaging and repeated examinations.

The underlying principle of contrast harmonic imaging is as follows: when microbubbles in the contrast agent are exposed to the ultrasound beams, they are disrupted or resonate, releasing many harmonic signals. When the tissue and microbubbles receive transmitted ultrasound waves, both produce harmonic components that are integer multiples of the fundamental frequency. A selective depiction of the second harmonic component visualizes signals from microbubbles, which are stronger than those from tissue because the harmonic content from microbubbles is higher than that from tissue [16]. Therefore, this technology can detect signals from microbubbles in vessels with a very slow flow without Doppler-related artifacts and is used to characterize vascularity [17].

There are many reports on the differential diagnosis of pancreatic masses using CE-TUS/CE-EUS, including solid and cystic masses [18,19,20,21,22,23,24,25,26,27,28,29,30,31,32,33,34,35,36,37,38,39,40,41,42,43,44,45,46,47,48,49,50,51,52,53,54,55,56,57,58,59,60,61]. However, the criteria for diagnosing malignancy in solid masses differ considerably from those for cystic masses, and it is therefore necessary to evaluate solid and cystic masses separately. For solid masses, it was reported that CE-TUS/CE-EUS is useful for the differential diagnosis of pancreatic cancer when a hypoenhancement pattern on CE-TUS/CE-EUS is defined as malignancy [20,21,22,23,24,26,27,28,29,30]. When a hypoenhancement tumor on CE-EUS and irregular contour on P-EUS was defined as malignancy, CE-EUS was significantly more accurate than P-EUS (respectively, sensitivity 90.8% vs. 95%; specificity; 74.6% vs. 42.9%; accuracy 85.8% vs. 78.9%, *p* < 0.001) [21]. Although there are several criteria for determining malignant cysts, including nodule morphology, vessel pattern in the nodule, and the presence of enhancement in a nodule [31,32,33,34,35], the presence of enhancement in a nodule may be preferred as the criterion because diagnostic criteria using the presence of enhancement in a nodule among these three kinds of criteria are simple and objective. It was reported that, in cystic masses, CE-EUS is useful for determining malignancy when a mass with an enhanced mural nodule on CE-EUS is defined as malignancy [31,34,35]. When the presence of mural nodule was defined as malignancy, CE-EUS was significantly more accurate than P-EUS (respectively, sensitivity 97% vs. 97 %; specificity; 75% vs. 40%; accuracy 84% vs. 64%, *p* = 0.0001) [31].

Although there are many retrospective studies on CE-TUS/CE-EUS, there are few prospective studies including solid/cystic masses. Therefore, we planned this prospective trial to confirm the advantages of P-TUS/P-EUS plus CE-TUS/CE-EUS over P-TUS/P-EUS alone in the diagnosis of pancreatic masses, including solid/cystic masses.

## 2. Methods and Design

### 2.1. Data Collection

Data are collected prospectively from all patients, and includes history, physical examination, laboratory data, pathological examination, clinical information, and adverse events. The study allocation, intervention, and assessment are adapted from standard protocol items (Figure 1).

### 2.2. Data Monitoring and Audit

The following aspects are monitored: data accumulation, patient eligibility, severe adverse events, protocol deviations, reasons for cessation or expiration of the protocol, background factors of the patients, and other problems concerning study progress and safety.

All study documentation and the source data/documents are accessible to auditors/inspectors, and questions are answered during inspections.

### 2.3. Images

To standardize the setting of processors and image interpretation, several discussions were held using movie clips of P-TUS/P-EUS and CE-TUS/CE-EUS before the initiation of the study. For P-TUS/P-EUS, tissue harmonic TUS/EUS is used for plain images. For CE-US/CE-EUS, the mechanical index is set at 0.18–0.2 and 0.2–0.4, respectively. After reconstitution with 2 mL of sterile water for injection, 0.015 mL/kg of the contrast agent is administered through a peripheral vein.

CE-CT is performed with the following settings: 64-row CT or more CT scanner, slice width ≤ 5 mm, and at least three phases (pancreatic parenchymal, portal, and delayed phases).

### 2.4. Final Diagnosis

The final diagnosis will be based on pathological findings obtained by EUS-FNA and/or surgery when the pathological diagnosis is malignant.

When pathological diagnosis is not malignant, the final diagnosis will be based on comprehensive diagnosis with imaging findings excluding CE-TUS/CE-EUS imaging, tumor markers, and pathological diagnosis.

### 2.5. Definitions

The diagnostic criteria were agreed following a discussion between 10 experts from 9 institutions before the clinical trial.

#### 2.5.1. Pancreatic Solid Mass

##### On P-TUS/P-EUS

A heterogeneous hypoechoic mass with an irregular contour on P-TUS/P-EUS is defined as malignancy.

##### On CE-TUS/CE-EUS

A hypoenhancement pattern on CE-US, in which the echo intensity of the mass is lower than that of the surrounding pancreatic tissue, is defined as malignancy.

##### On CE-CT

A hypovascular nodule on CE-CT is defined as malignancy.

#### 2.5.2. Cystic Mass

##### On P-US/P-EUS

A mass with a mural nodule on P-TUS/P-EUS is defined as malignancy.

##### On CE-TUS/CE-EUS

A mass with an enhanced mural nodule on CE-TUS/CE-EUS is defined as malignancy.

##### On CE-CT

A mass with an enhanced mural nodule on CE-CT is defined as malignancy.

### 2.6. Image Review

During blind reading, P-TUS/CE-TUS, P-EUS/CE-EUS, and CE-CT data are reviewed independently in a random order by 3 expert readers for each modality.

### 2.7. Primary Endpoint

The primary endpoints are to compare the diagnostic accuracies of P-TUS/P-EUS alone and P-TUS/P-EUS plus CE-TUS/CE-EUS for the diagnosis of pancreatic solid masses, and P-EUS/CE-EUS for cystic masses.

### 2.8. Secondary Endpoints

The secondary endpoints are comparisons of the diagnostic sensitivity and specificity of P-TUS/P-EUS alone and P-TUS/P-EUS plus CE-US/CE-EUS for pancreatic solid/cystic masses, and the accuracy of P-TUS alone and P-TUS plus CE-TUS for pancreatic cystic masses. Other secondary endpoints are comparisons of the diagnostic sensitivity, specificity, and accuracy of CE-TUS/CE-EUS and CE-CT for pancreatic solid/cystic masses. The safety, degree of effective enhancement, and diagnostic confidence obtained with the contrast agents will also be assessed.

### 2.9. Statistical Analysis

The assessments will be performed under fallback procedures. First, we will examine the superiority of the use of the contrast agent in EUS in the evaluation of the accuracy of the differential diagnosis of pancreatic cancer and non-pancreatic cancer, making comparisons with non-use of the contrast agent. This means that a one-sided alternative hypothesis H11: “the accuracy of CE-EUS for the differential diagnosis of pancreatic cancer and non-pancreatic cancer (accuracy rate) is higher than that of P-EUS” will be evaluated against the null hypothesis H01: “the accuracy of CE-EUS for differential diagnosis of pancreatic cancer and non-pancreatic cancer is equivalent to that of P-EUS.” This comparison will be made using McNemar’s test with a significance level of α1 = 0.0125. If the *p*-value is lower than the significance level α1, a significance level α2 for the assessment of the accuracy of CE-EUS in the differential diagnosis of pancreatic cancer and non-pancreatic cancer will be established as 0.025. By contrast, if the *p*-value is not less than 0.0125, a significance level α2 will be established as 0.0125. To determine the superiority of contrast agent use compared with non-use in the evaluation of the accuracy of CE-EUS for the differential diagnosis of pancreatic cancer and non-pancreatic cancer, a one-sided alternative hypothesis H12: “the accuracy of CE-TUS for the differential diagnosis of pancreatic cancer and non-pancreatic cancer is higher than that of P-TUS” will be evaluated against the null hypothesis H02: “the accuracy of CE-TUS for differential diagnosis of pancreatic carcinoma and non-pancreatic carcinoma is equivalent to that of P-TUS.” This evaluation will be made using McNemar’s test with a significance level of α2. If only the null hypothesis H01 is rejected in the above assessment, the results will be interpreted as meaning that the use of the contrast agent increases the accuracy of CE-EUS alone for the differential diagnosis. If only the null hypothesis H02 is rejected, it will be interpreted as meaning that the use of the contrast agent increases the accuracy of CE-TUS for the differential diagnosis. If both of the null hypotheses are rejected, it will be interpreted as meaning that the use of the contrast agent increases the accuracy of both CE-TUS and CE-EUS for the differential diagnosis. If any of the null hypotheses are not rejected, it will be interpreted as meaning that it cannot be said that the use of the contrast agent increases the accuracy of either CE-TUS or CE-EUS for the differential diagnosis (Figure 2).

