
### 2.10. Sample Size Calculation

#### 2.10.1. Pancreatic Solid Masses

The objective of this trial is to verify (1) that the accuracy of CE-EUS for the differential diagnosis of pancreatic cancer and non-pancreatic cancer is higher than that of P-EUS (superiority), and (2) that the accuracy of CE-TUS for the differential diagnosis of pancreatic cancer and non-pancreatic cancer is higher than that of non-contrast-enhanced P-TUS (superiority). To verify these co-primary endpoints, the fallback procedure in the gate-keeping strategy will be used.

Omoto et al. [21] reported diagnostic accuracy rates of 87.3% CE-EUS (with the use of the contrast agent plus non-use of the contrast agent; Combination) and P-EUS without the use of the contrast agent. According to the report, the accuracy rate was 87.3% for the former procedure and 78.9% for the latter procedure. Based on these results, a calculation was made, and the results showed that the proportion of a correct diagnosis by combination and an incorrect diagnosis by P-EUS was 10.3% (21/204 subjects) and the proportion of an incorrect diagnosis by combination and a correct diagnosis by P-EUS was 2.0% (4/204 subjects). It is assumed that similar results can be obtained in both TUS and EUS. To assure the familywise error rate (FWER) of 0.025 (one-sided alternative hypothesis), 0.025/2 = 0.0125 is assigned to Objective (1) and Objective (2).

Under the above setting, when the McNemar test is run on paired samples of the use and non-use of the contrast agent with a significance level of α = 0.0125 (one-sided) and 185 subjects as the minimum required number of subjects, the power 1-β is 0.840. For the fallback, if Objective (1) is significant, Objective (2) is assessed with a significance level of α = 0.025 (one-sided). In this case, the power 1-β is 0.902. In this study, the target sample size will be set at 232 subjects on the assumption that approximately 20% of subjects may be ineligible or not evaluable. The power 1-β under the target sample size of 232 subjects is 0.924 with a significance level of α = 0.0125 (one-sided), and 0.955 with a significance level of α = 0.0250 (one-sided).

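### The one-way fallback for the two solid-mass hypotheses is valid but gives away EUS power that Holm's procedure would recover at the same familywise error rate

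*Protocol article*

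**What the plan says.** Section 2.9 opens with "The assessments will be performed under fallback procedures", and section 2.10.1 confirms that "the fallback procedure in the gate-keeping strategy will be used". The rule for solid masses is:

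- **EUS (H01)** is tested first, "with a significance level of α1 = 0.0125". No later step raises this level.
- **TUS (H02) if EUS succeeds:** section 2.10.1 raises the level to 0.025.
- **TUS (H02) if EUS fails:** if the EUS p-value "is not less than 0.0125, a significance level α2 will be established as 0.0125".

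The running text of 2.9 names CE-EUS where it introduces the second test, but H12/H02 and section 2.10.1 show that TUS is meant.

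The FWER is 0.025 one-sided, split equally between the two objectives. Section 2.10.1 assumes similar results for the two modalities. It states power of 0.840 (level 0.0125) and 0.902 (level 0.025) at 185 subjects, and 0.924 and 0.955 at 232. The article gives no reason for letting alpha pass in one direction only.

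**The concern.** Once either hypothesis has been rejected at 0.0125, the stated FWER leaves room to test the other at the full 0.025. The plan uses this room for TUS and not for EUS. With p = 0.02 for EUS and p = 0.001 for TUS, the EUS objective fails. With the two p-values exchanged, both objectives succeed.

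The result runs against the ordering. The hypothesis placed first ends with lower power than the one placed second, although both start at 0.0125 and are assumed to have the same effect. At stake are a few points of power for EUS in solid masses. The Abstract reports the 301 patients as already enrolled, so those points can now come from the testing rule but not from recruitment.

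**Working it through.** **Inputs from section 2.10.1.** Discordant proportions: in favour of contrast, "was 10.3% (21/204 subjects"); against, "was 2.0% (4/204 subjects"). Evaluable minimum 185, target 232, loss about 20%. The correlation between the EUS and TUS test statistics is not given; I assume 0 to 0.8.

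**Step 1: reproduce the stated power.** I used the exact one-sided McNemar test, with the number of discordant pairs distributed as Binomial(n, 25/204).

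| n | level | stated | exact, 21/204 and 4/204 | exact, 10.3% and 2.0% |
|---|---|---|---|---|
| 185 | 0.0125 | 0.840 | 0.840 | 0.834 |
| 185 | 0.025 | 0.902 | 0.902 | 0.897 |
| 232 | 0.0125 | 0.924 | 0.928 | 0.924 |
| 232 | 0.025 | 0.955 | 0.958 | 0.955 |

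The stated powers reproduce, with the fractions at 185 and the rounded percentages at 232. Also 185/(1 − 0.2) = 231.25, rounded up to 232. The steps below use the stated powers.

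**Step 2: compare the rejection rules.** Write pE and pT for the EUS and TUS p-values.

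- EUS, fallback: pE < 0.0125.
- EUS, Holm: pE < 0.0125, or (pT < 0.0125 and pE < 0.025).
- TUS, both procedures: pT < 0.0125, or (pE < 0.0125 and pT < 0.025).

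Holm loses no rejection. It adds one region, 0.0125 ≤ pE < 0.025 with pT < 0.0125, where H01 is also rejected.

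**Step 3: error control under Holm.**

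- Both nulls true: an error needs pE < 0.0125 or pT < 0.0125, so its probability is at most 0.0125 + 0.0125 = 0.025 under any dependence. The fallback has the same error event.
- Only H01 true: an error needs pE < 0.025, so at most 0.025. With TUS power 0.84, the EUS type I error is about 0.023 to 0.025, against 0.0125 under the fallback.
- Only H02 true: the TUS decisions are the same in both procedures, so the error is also at most 0.025.

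**Step 4: power with equal effects and independent tests.**

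- EUS, n = 185: 0.840 + 0.840 × (0.902 − 0.840) = 0.892.
- TUS, n = 185, either procedure: 0.840 × 0.902 + 0.160 × 0.840 = 0.892.
- Both rejected, n = 185: fallback 0.840 × 0.902 = 0.758; Holm 0.758 + 0.052 = 0.810.
- EUS, n = 232: 0.924 + 0.924 × (0.955 − 0.924) = 0.953.

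**Step 5: power with correlated tests.** EUS power under Holm is P(EUS rejected at 0.0125) + P(0.0125 ≤ pE < 0.025 and pT < 0.0125), from a bivariate normal with the stated marginal powers.

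| correlation | EUS, n = 185 (fallback 0.840) | EUS, n = 232 (fallback 0.924) |
|---|---|---|
| 0 | 0.892 | 0.953 |
| 0.3 | 0.887 | 0.950 |
| 0.5 | 0.883 | 0.948 |
| 0.8 | 0.875 | 0.943 |

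The gain is 3.5 to 5.2 points at 185 and 1.9 to 2.9 points at 232.

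**Step 6: a weaker TUS effect.** Suppose TUS power at 0.0125 is 0.5 (my assumption). At n = 185 with independent tests, the gain is 0.5 × 0.062 = 0.031. At correlation 0.8 it is 0.004.

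**The case against.** The strongest reply is that nothing here is wrong. The fallback is a recognised procedure, it is fully specified, and it controls 0.025 for the two solid-mass hypotheses. The sample size was planned at 0.0125, so EUS has adequate power as written. All of that stands. A reader might infer that the plan's error control fails or that EUS is underpowered; the document supports neither. The 0.840 is also not a deficit peculiar to EUS, because it is the power of either test at 0.0125.

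A second reply is that the gain is conditional. Its upper end needs independent tests, although both modalities are planned in the same patients, and every figure in steps 4 and 5 assumes equal effects. Section 3 says that the authors know of no report comparing P-TUS with P-TUS plus CE-TUS, so the TUS effect is uncertain. This stands and limits the size of the gain, but not its direction: Holm never does worse.

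A third reply is that the change is not free. It is tempting to say that it has no downside, but the EUS conclusion would no longer stand apart from the TUS result, and EUS's own type I error could double from 0.0125 to 0.025 when TUS is truly effective. The stated FWER allows this, but it should be acknowledged. Relaxing a primary criterion after enrolment also needs clear dating, and the article does not say whether the reads have been analysed.

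The note to Figure 1 that the order of the modalities does not matter concerns the scheduling of examinations. It says nothing about the order of the hypotheses.

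**Conclusion.** The point holds as one of efficiency. For two hypotheses at 0.0125 each, Holm uniformly dominates the stated fallback at the same FWER bound, whatever the correlation between the tests. TUS power and the number of patients are unchanged.

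The size of the benefit rests on two assumptions: the plan's own of equal effects, and mine of a correlation between 0 and 0.8. Under both, the risk of missing a true EUS effect at 185 evaluable subjects falls from 16% to between 11% and 13%. The benefit is smaller at 232 subjects and could nearly vanish if TUS power is low and the tests are strongly correlated. The cystic comparison, with its own 0.025 in section 2.10.2, is unaffected.

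**What to change.** Add to section 2.9: *If H01 is not rejected at 0.0125 but H02 is rejected at 0.0125, H01 is re-tested at 0.025.* Add the matching return path to Figure 2. In section 2.10.1, keep 0.840 and 0.924 as the EUS power at 0.0125, and add the power under Holm with the assumed correlation and TUS effect stated.

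The cost is one sentence, one arrow and a short power statement, plus the two trade-offs above: the EUS conclusion waits for the TUS p-value, and its own type I error can reach 0.025. The change should be documented and dated before any accuracy results are known. If that is no longer possible, keep the fallback as written, since it is valid.

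### When only one of the two solid-mass nulls is rejected, the decision rule in 2.9 gives two opposite conclusions, and two of its sentences name CE-EUS where CE-TUS is meant

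*Protocol article*

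**What the plan says.** Protocol article, 2.9, sets out two one-sided tests for solid masses. H01 (CE-EUS no better than P-EUS) is examined first, by "McNemar’s test with a significance level of α1 = 0.0125". The level α2 for the second test is 0.025 if H01 is rejected. Otherwise, if the p-"value is not less than 0.0125, a significance level α2 will be established as 0.0125". H02 (CE-TUS no better than P-TUS) is then tested at α2.

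Four interpretation sentences follow:

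- The first begins "If only the null hypothesis H01 is rejected in the above assessment" and supports a claim for CE-EUS.
- The second gives the matching claim for CE-TUS when only H02 is rejected.
- The third supports both claims when both nulls are rejected.
- The fourth begins "If any of the null hypotheses are not rejected, it will be interpreted as meaning that it cannot be said" and denies an increase in accuracy for either CE-TUS or CE-EUS.

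On the modality attached to α2, 2.9 speaks of "a significance level α2 for the assessment of the accuracy of CE-EUS in the differential diagnosis" and introduces the second test with the words "To determine the superiority of contrast agent use compared with non-use in the evaluation of the accuracy of CE-EUS". Section 2.10.1 defines Objective (2) as CE-TUS against P-TUS and states that "if Objective (1) is significant, Objective (2) is assessed with a significance level of" 0.025 one-sided.

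**The concern.** These sentences turn two p-values into the trial's claim for solid masses. If exactly one null is rejected, the other is by definition not rejected. The first or second interpretation sentence then allows a claim, and the fourth withdraws it. The article does not say which takes precedence, and the fourth sentence comes last. Section 2.10.1 also calls the two objectives co-primary, a term that some readers take to mean that both must succeed. A one-null result could therefore be argued either way after the p-values are known, which a pre-specified rule is meant to prevent.

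The modality slip adds to the confusion, because the two affected sentences are the ones that allocate alpha to the second test.

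**Working it through.** **Step 1. Outcomes against rules.** Two nulls give four outcomes.

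| Outcome | First three sentences | Fourth sentence, read literally |
|---|---|---|
| H01 and H02 both rejected | claim for both | does not apply |
| only H01 rejected | claim for CE-EUS | no claim for either |
| only H02 rejected | claim for CE-TUS | no claim for either |
| neither rejected | no rule | no claim for either |

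The two middle rows conflict. Only the last row lacks a rule without the fourth sentence.

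**Step 2. Reproducing the stated powers.** Inputs from 2.10.1 are discordant proportions 21/204 and 4/204, N = 185 and 232, and one-sided α = 0.0125 and 0.025. The total discordant proportion is 25/204 = 0.1225, and the favourable share among discordant pairs is 21/25 = 0.84. Power of the exact McNemar test is the sum over m of P(m discordant pairs out of N) × P(B ≥ c_m), where B is binomial(m, 0.84) and c_m is the smallest count whose upper-tail probability under binomial(m, 0.5) is at most α.

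| N | α | Stated | Exact, from the fractions | Exact, from 10.3% and 2.0% |
|---|---|---|---|---|
| 185 | 0.0125 | 0.840 | 0.840 | 0.834 |
| 185 | 0.025 | 0.902 | 0.902 | 0.897 |
| 232 | 0.0125 | 0.924 | 0.928 | 0.924 |
| 232 | 0.025 | 0.955 | 0.958 | 0.955 |

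The stated powers hold. The inflation also holds: 185/0.8 = 231.25, rounded up to 232.

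**Step 3. Alpha.** 0.0125 + 0.0125 = 0.025. Under the global null with independent tests, the chance of at least one rejection is 0.0125 + 0.9875 × 0.0125 = 0.0248. With α2 applied to CE-TUS, the familywise rate is kept.

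**Step 4. Chance of any claim under each reading.** Let p1 be the power for EUS at 0.0125, p2 the power for TUS at 0.025, and p2* the power for TUS at 0.0125. Section 2.10.1 assumes the same effect in both modalities, so p2* = p1.

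- Literal reading (both nulls must fall): P(both) = P(EUS at 0.0125 and TUS at 0.025).
- Fallback reading (at least one falls): p1 + p2* − P(EUS and TUS both at 0.0125).

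Independent tests, N = 185:
- both: 0.840 × 0.902 = 0.758
- EUS only: 0.840 × 0.098 = 0.082
- TUS only: 0.160 × 0.840 = 0.134
- at least one: 1 − 0.160² = 0.974

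Independent tests, N = 232:
- both: 0.924 × 0.955 = 0.882
- EUS only: 0.924 × 0.045 = 0.042
- TUS only: 0.076 × 0.924 = 0.070
- at least one: 1 − 0.076² = 0.994

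The article gives no correlation between the EUS and TUS tests, so a range is assumed. For correlation 0.5, the joint probabilities come from a bivariate normal distribution with the stated powers as margins. At perfect correlation, P(both) is the smaller of p1 and p2, and the fallback probability is p1.

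| N | Assumed correlation | At least one claim, fallback | Any claim, literal | Difference (one-null outcomes) |
|---|---|---|---|---|
| 185 | 0 | 0.974 | 0.758 | 0.217 |
| 185 | 0.5 | 0.937 | 0.786 | 0.151 |
| 185 | 1 | 0.840 | 0.840 | 0 |
| 232 | 0 | 0.994 | 0.882 | 0.112 |
| 232 | 0.5 | 0.978 | 0.894 | 0.084 |
| 232 | 1 | 0.924 | 0.924 | 0 |

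The last column is the share of outcomes for which 2.9 gives two opposite conclusions.

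**Step 5. The α2 label.** Section 2.9 attaches α2 to CE-EUS, but H12 and H02 as written there concern CE-TUS, and the text then applies α2 to that test. Section 2.10.1 gives 0.025 to Objective (2), which is CE-TUS. The operative test and level agree in both sections. Only the connecting words are wrong.

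**The case against.** The strongest reply is that the intended meaning is not in real doubt. The first three interpretation sentences cover every outcome but one, so the fourth must be meant for that one. Read literally, it would cancel two sentences just written and leave the alpha split without a purpose. The per-objective powers in 2.10.1 also fit only an either-or rule. Figure 2, which the fourth sentence cites, is not available here and may state the rule correctly. All of this stands, and it is why the point is a contradiction in wording and not a flaw in the design. It does not remove the conflict from the text, which is easily settled now and harder to settle neutrally once results are known.

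Two stronger readings are tempting, and the documents support neither:

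- A reader might infer that the trial has an all-or-nothing rule and so loses up to 22 percentage points in the chance of a claim. The named fallback procedure and the 0.0125 + 0.0125 split contradict this. The 22 points are also the independence extreme. Both tests use the same type of cohort and final diagnosis, so positive correlation is plausible and would shrink the gap.
- A reader might infer from the CE-EUS label that CE-EUS may be tested again at 0.025, with inflated error. Under 2.9, 0.025 becomes available only after CE-EUS has already passed at 0.0125. If it has not passed, α2 is 0.0125, the level it has just failed. No CE-EUS result could change.

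**Conclusion.** The point holds as an inconsistency in the primary decision rule. A result in which exactly one null is rejected receives two opposite conclusions in 2.9, and the context indicates that the fourth sentence was meant for the case where neither is rejected. The modality slip is a labelling error that the rest of 2.9 and 2.10.1 resolve.

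The conflict affects between 0 and about 22% of outcomes at N = 185, and between 0 and about 11% at N = 232. These figures rest on the stated powers, equal effects in TUS and EUS as 2.10.1 assumes, and a non-negative correlation, which has to be assumed. The N = 232 figures also suppose none of the planned loss of about 20%. If TUS gained less than EUS, EUS-only results would be more frequent than shown. The contradiction itself depends on none of these assumptions.

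**What to change.** Make three wording corrections in 2.9:

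1. Begin the fourth interpretation sentence with *If neither null hypothesis is rejected*.
2. In the sentence that sets α2, replace CE-EUS with CE-TUS.
3. In the sentence that introduces H12, replace CE-EUS with CE-TUS.

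Then check Figure 2 against the corrected text. The abstract reports the patients as already enrolled, so the correction should be recorded and dated before analysis. It costs nothing in patients, data, alpha or power.
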